## Abstract

**Objectives/Aim:**

To adapt a structured behavioural support intervention for smokeless tobacco (ST) cessation and to assess the feasibility and acceptability of delivering the intervention via dentists within dental settings in Pakistan.

**Material and methods:**

The study will have 3 phases: (1) Adapt a previously developed intervention to make it suitable for delivery in a clinical/dental setting through qualitative interviews with dental patients and dentists; (2) A multi-centre, pilot randomised control trial in two teaching dental hospitals in Pakistan. Participants (dental patients) will be randomly assigned to intervention or control group in a 1:1 allocation ratio to receive either a structured behavioural support intervention involving face to face counselling or self-help material plus usual care. Each participant will be in the study for approximately 6 months and the overall study is expected to run for 12 months; (3) An embedded qualitative process evaluation. All trial participants will be followed up at 3 and 6 months to assess self-reported ST use. Outcome measures will include: rates of eligibility, recruitment and retention, randomisation group cross-over rates, the provision of data on ST use behaviour, fidelity to the intervention and qualitative assessment of acceptability and feasibility.

**Discussion:**

Despite the high use of ST in Pakistan, users are offered negligible cessation support. The findings of this multi-centre, mixed-method feasibility study will inform the scope for a larger trial on ST cessation delivered through the existing dental health system.

## Introduction

More than 85% of the global smokeless tobacco (ST) users live in the South and South-East Asian region [1, 2]. The use of ST in Pakistan, a South-Asian country, has deep-rooted cultural and traditional ties. ‘Pan’, largely considered as an occasional delicacy, is often a part of the festive celebrations and is consumed by young and old, irrespective of gender. ‘Naswar’, the most popular ST product in Pakistan, is sold openly to minors in transparent bags, without any health warning [3]. Despite the alarmingly high rates of use and evidence on the associated health harms, such as oral cancers [4], oral pre-malignant lesions [5] and fatal strokes [4], ST control in Pakistan remains largely neglected.

While many tobacco users wish to quit, the majority fail to do so. Dependence on tobacco makes it challenging to quit and support for cessation is often minimal in most countries [6, 7]. According to the ‘Global adult tobacco survey’ GATS Pakistan (2014), 21.1% of the ST users made a quit attempt in the past year. In more than half of the cases, this was an un-assisted quit attempt (50.8%). Of the 43.3% of ST users and 42.9% of tobacco smokers who visited a health care provider, only 33.7% ST users and 51.8% of the tobacco smokers were offered quit advice by healthcare providers respectively [8]. These figures are clearly reflective of the gap between the need and availability of cessation support offered to tobacco users (especially ST users) in Pakistan.

Despite substantial evidence on the effectiveness of affordable tobacco cessation interventions at both the individual and population level [9, 10], progress in implementing Article 14 of the Framework Convention on Tobacco Control (FCTC), pertaining to tobacco cessation, has been slow, especially in low and middle income countries (LMICs) [11]. Despite being a signatory of the FCTC since 2005 [12], Pakistan lags behind its neighbouring countries in terms of ST control laws and alignment of the existing laws with FCTC guidelines. ST control remains largely neglected against the backdrop of the challenges that Pakistan faces with implementation and enforcement of key measures for smoked tobacco [3, 13]. ST products in Pakistan are not taxed, the contents are not regulated and the users are offered negligible cessation support.

Like many LMICs, Pakistan lacks resources to effectively address the multiple health problems it faces, which is one of the main challenges in treating tobacco dependence [13, 14]. However, the existing health system (such as dental settings) can be effectively engaged to extend its role to tobacco control with minimum investment [15]. This multi-centre mixed-method feasibility study aims to adapt a behaviour support intervention for ST cessation and assess the feasibility and acceptability of delivering the intervention via dentists within dental settings in Peshawar, Pakistan.

## Material and methods

### Study design

We plan to conduct a mixed-method feasibility study with an incorporated multicentre, randomised, controlled pilot study. The Randomised Control Trial (RCT) protocol conforms to the Standard Protocol Items: Recommendations for Interventional Trials (SPIRIT) and the Consolidated Standards of Reporting Trials (CONSORT) statement for reporting RCTs. The aim of this study is to adapt a previously developed structured behaviour support intervention for ST use cessation and assess the feasibility and acceptability of delivering it in dental hospitals via dentists.

The study will be conducted in three phases. In phase 1, qualitative work will be undertaken to inform the adaptations required to the intervention resources, to prepare the training workshop and module for the participating dentists and to inform the trial design. The intervention that will be adapted and tested in this study, is a structured, theory-based behavioural support intervention for ST cessation, known as BISCA, ‘Behavioural support Intervention for Smokeless Tobacco Cessation in South Asians’. BISCA is a behavioural support intervention for ST cessation which was originally developed in the UK for South-Asian community [16]. The intervention was piloted in four NHS Stop Smoking Services (Leicester, Leeds, Bradford and Tower Hamlets) in the UK (amongst ST users of South Asian origin) and in a community setting in Karachi, Pakistan and was found feasible and acceptable to deliver [16]. It has also been adapted to meet the needs and cultural context of ST users in Bangladesh, India and Pakistan [17].

While the intervention has been tested in community settings with ST users in South-Asia, it has not been tested in hospital/clinical settings in this region. Before delivering it in routine dental practice via dentists it is important to understand the views of dental patients who are users, on their ST use initiation, continued ST use, cessation attempts and their views on the intervention resources. It is also important to understand the range of issues influencing delivery and integration of behavioural support in routine dental practice and to make necessary adaptations to make it suitable for delivery in routine dental practice. The aim is to retain the core components relating to the effectiveness of the intervention, whilst making appropriate changes that will enhance its acceptance in a dental/clinical setting. For this purpose, interviews with dentists working at the study sites and dental patients ‘who use ST’ and are visiting the study site will be undertaken.

In phase 2, the intervention will be delivered through a multi-centre, randomised, controlled pilot trial in which participants (dental patients who are ST users) will be randomly allocated to two arms: intervention and control (self-help material) with 1:1 allocation ratio. Phase 3, will involve an embedded qualitative study, within the pilot trial, after the intervention delivery is complete, to gain in-sight into the views of the trial participants regarding the feasibility and acceptability of the intervention and the trial procedures. The project is expected to run for approximately 12 months.

### Trial registration

ISRCTN: Study ID ISRCTN18072109; 10.1186/ISRCTN18072109 registered 13. January, 2022. Data collection started on 23, October 2021.

### Study sites

This study will be carried out in Peshawar, which is the capital city of Khyber Pakhtunkhwa (KP), the north-western province of Pakistan, where the use of Naswar is most common. The study will be conducted at two specialised tertiary level, dental teaching hospitals in Peshawar: a public sector facility, the Khyber College of Dentistry (KCD); and a private sector facility, the Sardar Begum Dental College (SBDC). Being the only public sector specialized dental hospital in Peshawar, KCD caters to most of the urban and rural population of Peshawar as well as nearby areas.ST use has been linked to low socioeconomic status and since services are offered at nominal rate at KCD, it is believed that most of the patients visiting this hospital belong to low socioeconomic class. It is hoped, that the choice of this site will make patient recruitment easier. In order to explore how intervention delivery varies across public and private hospitals, SBDC has been selected as the 2nd study site. Both the study sites have expressed their support for the study in writing by issuing ‘letter of support’ signed by the deans of the hospitals.

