### Analysis

As recommended, the analysis of this feasibility study will be limited to descriptive statistics to make comparisons between the intervention and control group [23, 29–31]. Baseline data such as dependency scores will be measured as mean and standard deviations (SDs), while categorical data, will be reported as counts and percentages. Similarly, feasibility outcome measures, will be measured as rates/proportions and will be reported with 95% confidence intervals (CIs). Whereas, fidelity index, will be expressed as mean and SD. Quit rates and dependency scores between the two groups will be compared and association between quit status and socioeconomic variables will be determined. All interviews will be, audio-recorded and transcribed verbatim. Thematic analysis will be used to analyse the transcripts, using framework analysis approach. The analysis will be done in Microsoft Excel and NVivo-11 software.

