
Box 1 Strengths and limitations of this study
First study using a randomised controlled design to assess the feasibility and acceptability of a structured behaviour support programme for smokeless tobacco cessation delivered via dentists in routine dental practice in Pakistan.Evidence of implementing behaviour cessation via dentists in Pakistan will be established.This study will address an important evidence gap regarding the feasibility of dentists in tobacco cessation in a low middle income country.The multicentre design including patients from two tertiary level teaching hospitals in Pakistan comparing two feasible strategies will support external validity and implementation.Owing to the type of interventions, blinding of the patients and intervention providers is not possible.

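### The second hospital is included to explore public versus private delivery, but no stated outcome, analysis or recording rule is linked to hospital

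*Protocol article*

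**What the plan says.** The Study sites section of the protocol article names a public hospital (KCD) and a private one (SBDC). It gives one reason for the second: to "explore how intervention delivery varies across public and private hospitals".

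The Analysis section says the quantitative work "will be limited to descriptive statistics to make comparisons between the intervention and control group". Feasibility outcomes are rates or proportions with 95% confidence intervals. For delivery itself, the "fidelity index, will be expressed as mean and SD". It adds: "Quit rates and dependency scores between the two groups will be compared and association between quit status and socioeconomic variables will be determined". Interviews are analysed thematically with a framework approach. The Outcomes section lists eligibility, recruitment, retention, tobacco-use data, fidelity and qualitative acceptability. Hospital appears in neither section.

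Under Data collection and outcome measures, audio recording covers the visits of the first 10% of patients in both arms. These recordings serve both fidelity and cross-over, and no division between hospitals is given. Under Participants and sampling, the phase 3 interviews draw the same number of respondents from each hospital, and the aim is to interview every dentist who delivered the intervention. Under the randomisation heading, the hospital's name is on each allocation envelope.

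**The concern.** A design decision is justified by a question that the stated outcomes and analysis do not take up. Pooled results cannot show variation between hospitals. A pooled rate can match expectation while one hospital does poorly, and a definitive trial planned on it would not know.

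The recording rule is a separate matter because it affects data collection. A table by hospital can be added at any time from data already held, but recordings not made at one hospital cannot be recovered.

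The wording of the aim also asks more than two hospitals can give. With one per sector, sector cannot be separated from hospital. The Study sites section itself expects most KCD patients to be of low socioeconomic class, so patient mix is entangled as well.

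**Working it through.** **Inputs.** From Participants and sampling: 30 or more per arm, 36% attrition, 50 recruited per arm. From Data collection: the first 10% of patients recorded. The split between hospitals is not stated; an even split is assumed and varied below.

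**The plan's own figure.** 30 / (1 − 0.36) = 46.9, so at least 47 per arm. The stated 50 leaves 50 × 0.64 = 32, which meets the target of 30 or more. The sample size is consistent and is not at issue.

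**Where hospital appears.**
- Study sites: as the reason for including SBDC.
- Phase 1 and phase 3 sampling: in the numbers interviewed.
- Randomisation: on the envelope.
- Outcomes and Analysis: nowhere.

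Hospital is therefore known for each randomised participant, but no stated summary uses it.

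**What a pooled rate can hide (invented illustration).** With 50 patients per hospital, 40 retained at one (80%) and 24 at the other (48%) give 64 of 100. That is the 64% implied by 36% attrition, despite a 32-point gap.

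**Precision of retention at 64%.**
- Pooled, n = 100: Wilson 95% interval 54.2% to 72.7%.
- One hospital, n = 50: 1.96 × √(0.64 × 0.36 / 50) = 0.133, about ±13 points (Wilson 50.1% to 75.9%).
- Between-hospital difference, 50 and 50: 1.96 × √(0.64 × 0.36 × (1/50 + 1/50)) = 0.188, about ±19 points.
- With 70 and 30: 0.205, about ±21 points.

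Only large differences would be visible. These widths apply to retention; eligibility and recruitment have other denominators.

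**Fidelity.** 10% of 100 is 10 recorded patients, about 5 of them in the intervention arm and so two or three per hospital. For 3 against 2 patients, the 95% half-width for a difference in means is t(0.975, 3 df) × √(1/3 + 1/2) = 3.18 × 0.913 = 2.9 SD, which is almost uninformative.

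**Chance that all 5 recorded intervention patients come from one hospital**, if each patient's hospital is independent with KCD share p: p⁵ + (1 − p)⁵.
- p = 0.5: 6%.
- p = 0.7: 17%.
- p = 0.8: 33%.

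**Cross-over.** It is read from the same recordings, so the denominator is about 5 per hospital, not 50. With none seen in 5, the exact upper 95% limit is 1 − 0.025^(1/5) = 52%.

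**The case against.** The strongest reply is that this is a condensed article. A descriptive table by centre is commonly left to the full protocol or analysis plan, so its absence here does not show that none is planned. That stands, and it keeps the point minor. It does not cover the recording rule, which the article states and which does not secure both hospitals. Nor does it cover the wording of the aim.

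Three stronger readings might be inferred, and the documents do not support them.

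- **That the analysis compares only the two arms.** It also has feasibility rates, fidelity, an association with socioeconomic variables and framework analysis. Eligibility and recruitment precede randomisation, so they cannot be arm comparisons, and the arm sentence cannot exclude other descriptive summaries.
- **That the trial cannot answer its question.** The promise is only to explore. Equal interviewing at each hospital and interviews with all delivering dentists are a plausible route to a qualitative comparison, although none is stated.
- **That Box 1 claims a sector effect.** It says "comparing two feasible strategies will support external validity and implementation", but the strategies are the trial arms and Box 1 mentions no sector.

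It is also fair to say that retention is not delivery, and that fidelity, the direct measure, is too sparse for an interval by hospital. The fix below allows for this.

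**Conclusion.** The point holds as a mismatch between a stated purpose and the stated outcomes and analysis, and it is minor. As written, no result is linked to hospital, the recordings may miss one hospital, and a difference between one public and one private hospital could not be read as a sector effect.

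On an even split with 64% retention, per-hospital rates are usable as description only. Fidelity and cross-over by hospital would be little more than case description. The size of the recording problem depends on the unstated split: a 6% to 33% chance of no intervention recordings at one hospital, for KCD shares from 50% to 80%. The article hopes that choosing KCD will ease recruitment, so an uneven start is plausible but not established.

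**What to change.** 1. **Analysis section:** report eligibility, recruitment, retention and cross-over for each hospital as well as pooled, with 95% confidence intervals and denominators, labelled exploratory.
2. **Analysis section:** state that the phase 3 interviews will be read by hospital.
3. **Data collection:** keep the same number of recordings but spread them over both hospitals, for example the first 10% at each. Describe fidelity by hospital without a between-hospital interval.
4. **Study sites:** word the aim as variation between these two hospitals, one public and one private.
5. **Box 1:** leave unchanged.

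The cost is a few table rows and some sentences. The rates use data already planned, and only the choice of which visits to record changes. The downside is wide per-hospital intervals: about ±13 points for retention on an even split, and far wider for cross-over.

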### Participants and sampling

*Phase 1:* Qualitative research does not aim to seek findings that are representative. Therefore, in line with good practice recommendations for qualitative research, a non-probability sampling approach will be adopted for purposively selecting dentists and patients. Dental patients and dentists will be purposively selected from the selected hospitals. We anticipate interviewing 10–12 dental patients and 10–12 dentists. The reason behind this sample size for dentist’s interview is, that we aim to interview the senior- most dentist from each of the five specialities of dentistry, from each of the two study site (prosthodontics, periodontics, oral medicine, operative dentistry and maxillofacial surgery). The choice of interviewing senior faculty is based on the assumption that, they would have immense experience of treating dental patients and hence would have had a fair experience of interacting with dental patients who are ST users; for whom the intervention is to be delivered. Furthermore, senior faculty are the administrative heads of their speciality, which is why these dentists are responsible for deciding the standard operating procedures for their respective departments. It is also believed that their views would be reflective of the entire department that they run. The criteria for dental patients will be, those patients visiting the study site(s) for a dental treatment and are current ST users. The reason behind the anticipated sample size for the patient’s interviews is that we aim to recruit 5–6 patients from each study site. These will be purposively selected to ensure there is the sample diversity that qualitative research requires. This means that we recruit across both genders and different age groups ranging from (18–78 or more years) using an age bracket of 15 years and therefore taking at least one patient from each 15 years bracket, from each study site. The reason for including different age groups is based on the assumption that, the users belonging to different age groups will have varying degree of exposure to ST because of the length of habit. In most cases, users start using ST in early adulthood and over the years their habits change. Regarding gender, while we aim to interview female respondents, based upon evidence from previous research, we are not very optimistic on being able to do so. No female ST users were interviewed in a recent qualitative study on ST cessation in Peshawar [17]. While the use of ST is common, it is not common for women in Peshawar to disclose this. Therefore, we anticipate a female representation of 20% (from any age bracket).

*Phase 2 and 3:* The trial participants will be recruited from the periodontology and prosthodontics departments of the selected hospitals. The choice of recruitment of dental patients from periodontology and prosthodontics is based on practical as well as biological grounds. ST use, is a potential risk factor for periodontal changes, such as gingival recession [18], attachment loss [19, 20], which can contribute towards tooth loss. Therefore, it is believed that a substantial number of patients using ST, will be visiting these departments. Furthermore, in most cases, patients referred to these departments require multiple visits for the completion of their treatment. However, if we are unable to recruit the required sample size within the stipulated time, then recruitment will be done from the department of ‘operative dentistry/endodontics’ as well.

Participants will be dental patients visiting SBDC/KCD, for a dental treatment and who are 18 years and above, are regular ST users, are willing to visit the study site for three visits and willing and able to provide written or thumbprint informed consent. Patients who are currently accessing cessation support or/and are unable/unwilling to provide written or thumbprint informed consent will be excluded. The intervention will be delivered by consenting, licensed dentists, working as faculty members or post-graduate trainees, at the selected wards/department of KCD and SBDC. These dentists will be trained in intervention delivery prior to the recruitment of patients.

In line with good practice recommendations, no formal sample size calculation has been completed for this pilot study [21]. Recommendations suggest, sample sizes of 30 or more participants in each arm [22, 23]. We anticipate an attrition rate of 36% from a similar feasibility trial [16] and hence, aim to recruit 50 participants in each arm.

An embedded qualitative process evaluation (phase 3) will be undertaken for which some of the trial participants and participating dentists will be invited, for face-to-face interviews, after completion of all trial visits. The purpose of these interviews is to qualitatively assess, the acceptability and feasibility of the intervention. A non-probability sampling approach will be used and at this stage it is anticipated that 10–12 patients who participated in the trial will be interviewed. Taking 5, 6 patients from each study site and at least 1 patient from each of the 15 year age bracket, from 18–78 years; as stated above in phase 1. As for the dentists, we anticipate interviewing 10–12 dentists who participated in the trial. It is anticipated that at least, 2–3 dentists will participate from each department, since we propose to conduct the trial in two departments at each study site, providing approximately 8–12 dentists in total. We aim to interview all dentists who participated in the intervention delivery. Equal number of respondents will be selected from each of the two study sites.

